## 2.2 Objectives

We seek to:

1. Estimate vaccine effectiveness against the composite outcome of COVID-19 hospitalisation/death as a function of time since first SARS-CoV-2 vaccine dose and pool these estimates for the whole UK population.
2. Assess if vaccine effectiveness as a function of time since first vaccine dose differs by vaccine type, age group and sex.

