## 5.4 Potential effect modifiers

Stratification into different population groups by age group (18-64, 65-79, 80+ years) and sex will be performed. Given that vaccine effectiveness may differ amongst previously infected individuals, we will stratify analyses by previous confirmed infection status when adequate numbers are available for meaningful statistical analysis. As noted above, we will also stratify analyses by vaccine type.

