### 5.5.2 Matched analysis

To create control groups for our primary analysis, we will emulate a ‘target trial’. We will do this by conducting 1:1 risk-set matching to identify individuals who had not yet become exposed (i.e. remained unvaccinated) on the date an exposed person received their vaccine dose. We will do this using a time-varying propensity score matching algorithm, by fitting separate propensity score models by month.

Due to the strong confounding effect of living in an elderly care home (arising from the targeted vaccination of these residents and their high risks of COVID-19 harms) and the lack of available controls, we will exclude people whose household had more than 10 people with an average age of 65 years and over. This will be used as a proxy for those living in an elderly care home.

We will incorporate the following characteristics into the time-varying propensity score model: sex, age (grouped in 5 year bands), SES, number of risk factors (grouped), number of previous SARS-CoV-2 tests pre-vaccination era (grouped), geography (local authority level), urban-rural settlement, average household age, number of people in household (grouped), smoker indicator, BMI (grouped), presence in hospital status (hospitalised for any reason 4 weeks prior to monthly time-period) and previous positive test indicator (tested positive previous to monthly time-period). Individuals will then be matched using exact matching based on the propensity score in 1% bands, local authority, and age (exact age in years, truncated up to 100 years). The adequacy of the matching will be assessed by checking for imbalance of the individual covariates and the individual risk groups across exposure groups.

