We expect that any effects before 14 days for first dose vaccination will reflect programmatic effects (e.g. being instructed not to attend vaccination if symptomatic and reinforcement of behavioural advice to reduce COVID-19 related risks). Follow up will therefore start from day 14 after the date of first dose vaccination (and day 7 after second dose) for both the exposed and control person. It will end for both the exposed and control person on the first of: experiencing the outcome of interest, death (from any cause) or end of follow up period. Unvaccinated controls who become vaccinated will be eligible to become considered as exposed, after follow up is censored for the exposed-unexposed pair at the date of vaccination of the control. Follow-up of the exposure period will also be censored for both the recipient and the control if the partially vaccinated recipient participant received a second dose. Analyses will be stratified by vaccine type.

For the matched cohort analysis, we will draw Kaplan Meier curves to inspect cumulative incidence. We will then fit Poisson regression models to estimate rate ratios (RRs) with 95% confidence intervals (95% CIs) for the association between exposure group and risk of the outcomes, at weekly time periods from exposure to event (Section 4.2).

We will fit a model including a spline with person-time defined in days, to explore the timing of any waning of vaccine effectiveness. The splines will be fit using thin plate regression splines (the R package ‘mgcv’ default settings) with weekly knots from days 14 to the maximum week. The difference between the smooths in the exposure groups will be calculated using methods by Simpson, [7] to obtain smoothed estimated RRs between the exposure groups at daily follow-up periods.

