### 5.5.4 Sub-group analysis

Subgroup analyses by vaccine type, age group and sex will be performed. We will consider conducting sub-group analysis by time-period too, especially if there is evidence of different circulating variants predominating.

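### Objective 2 has no test of difference, and the all-age matched waning curve has no exposure-by-age term, so a changing age mix could mimic or mask waning

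*SAP*

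**What the plan says.** Objective 2 (SAP 2.2) poses a question of difference: "Assess if vaccine effectiveness as a function of time since first vaccine dose differs by vaccine type, age group and sex". The analysis offered for it is separate fitting. Section 5.4 says "Stratification into different population groups by age group (18-64, 65-79, 80+ years) and sex will be performed" and section 5.5.4 says "Subgroup analyses by vaccine type, age group and sex will be performed". Neither names an interaction test, a heterogeneity test or any other rule for deciding that curves differ, and 5.5.5 gives multiplicity as not applicable.

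The matched Poisson model (5.5.2) is described as "We will then fit Poisson regression models to estimate rate ratios (RRs) with 95% confidence intervals (95% CIs) for the association between exposure group" and the outcomes, by week since exposure. The spline and quadratic waning models in the same section are described by exposure group and days. The only stratification stated there is "Analyses will be stratified by vaccine type". Pairs are matched exactly on propensity band, "local authority, and age (exact age in years, truncated up to 100 years"), and follow-up is "censored for the exposed-unexposed pair at the date of vaccination of the control". It also ends for both members if the recipient has a second dose. The study ends on 30 April 2021 (3.1).

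The supply table for pooling (5.6.4) is laid out by vaccine, single-day period and age group. It has no sex column.

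**The concern.** There are two linked gaps.

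First, a stated objective has no matching inference. Curves fitted separately by age, sex or vaccine do not show whether they differ, and nations cannot pool sex-specific results from a table without sex.

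Second, a waning claim compares one follow-up period with another. Matching and joint censoring make the two arms comparable within a period. They do not make the people contributing at day 70 comparable with those contributing at day 14. If effectiveness varies by age and the age mix of events shifts along follow-up, the all-age rate ratio moves although no age group's effectiveness has changed. Section 5.5.2 also judges maintained effectiveness by a point estimate against 0.5, so a modest shift can change the reading.

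**Working it through.** The SAP gives no design figure for this point, so there is none to reproduce. The checks below use its tables plus assumptions marked as such.

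**1. Who can contribute late.** 30 April 2021 minus 70 days is 19 February 2021; minus 14 days is 16 April. Day 70+ comes only from people vaccinated by 19 February, while days 14-20 can include people vaccinated up to 16 April.

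**2. Distance from 0.5.** Inputs are the events from day 14 in the matched table of 5.6.2. Pairs are 1:1 with near-equal person-time, so RR ≈ recipient events / control events.
- BNT162b2: 238/488 = 0.488 (printed rates: 2.4/5.0 = 0.480).
- ChAdOx1: 303/541 = 0.560 (2.2/4.0 = 0.550).
- Both: 541/1029 = 0.526 (2.3/4.4 = 0.523). SE of log RR = √(1/541 + 1/1029) = 0.053, giving a 95% CI of 0.474 to 0.583.

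BNT162b2 lies 0.012 below 0.5 and ChAdOx1 lies 0.060 above it. These are averages over follow-up, not weekly values.

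**3. Drift with no true waning.** With pairs censored together, the all-age RR in period t is Σ s(a,t) × RR(a), where s(a,t) is age group a's share of control events. RR(a) is held constant over time.

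From the SAP: 1,680,152, 691,534 and 202,188 pairs aged 18-64, 65-79 and 80+, and 1029 control events. (The count table just above gives 1,650,185 matched recipients; the characteristics table is used because it carries ages and events.)

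Assumed: first doses on days 10-50 (80+), 35-75 (65-79) and 60-130 (18-64) after 8 December; 3% of pairs censored per day; baseline event-rate ratios of 1:3:10 or 1:5:25 across the age groups from youngest to oldest.

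| RR at 18-64 / 65-79 / 80+ | Baseline | Days 14-20 | Day 70+ | Drift |
|---|---|---|---|---|
| 0.50 / 0.50 / 0.50 | both | 0.50 | 0.50 | 0 |
| 0.45 / 0.50 / 0.60 | 1:3:10 | 0.521 | 0.555 | +0.034 |
| 0.45 / 0.50 / 0.60 | 1:5:25 | 0.542 | 0.566 | +0.024 |
| 0.40 / 0.50 / 0.70 | 1:3:10 | 0.543 | 0.610 | +0.067 |
| 0.40 / 0.50 / 0.70 | 1:5:25 | 0.584 | 0.632 | +0.048 |
| 0.60 / 0.50 / 0.40 | 1:3:10 | 0.493 | 0.447 | −0.046 |
| 0.60 / 0.50 / 0.40 | 1:5:25 | 0.466 | 0.435 | −0.031 |
| 0.40 / 0.50 / 0.70, no age staging | 1:3:10 | 0.541 | 0.541 | 0 |

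Example, fourth row, day 70+: control-event shares are 0.03, 0.40 and 0.57, so 0.03×0.40 + 0.40×0.50 + 0.57×0.70 = 0.611 (0.610 with unrounded shares).

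**4. Effect on the quadratic test.** A Poisson model with group, day, day squared and their interactions was fitted to these expected counts. The between-arm quadratic term has expected z of 0.08 to 0.17 in the four upward-drift rows and about −0.1 in the reversed rows.

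**5. What a test of difference would look like.** Ratio of RRs, ChAdOx1 to BNT162b2, from day 14: 0.560/0.488 = 1.15. SE of its log = √(1/238 + 1/488 + 1/303 + 1/541) = 0.107, giving a 95% CI of 0.93 to 1.42 and p = 0.20. This ignores time and age. Age matters here: 80+ makes up 2.7% of BNT162b2 pairs and 10.3% of ChAdOx1 pairs; 65-79 makes up 38.4% and 21.4%. The same test by age cannot be run because the SAP prints no events by age.

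**The case against.** Section 5.4 plans age stratification without limiting it to secondary analyses, and the 5.6.4 table already collects age-specific daily counts. Age-specific curves would therefore expose a drift, and the absence of an age term is partly an inference from silence. Exact age matching with joint censoring removes age confounding within every period. The secondary whole-cohort model (5.5.3) adjusts for age and time period. Events are also too sparse for rich interactions: 541 recipient events over 9 periods, 3 age groups and 2 vaccines average about 10 per cell, or about 5 after splitting by sex.

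Much of this stands. It limits the size of the problem and rules out a heavy remedy. It does not close the gap, because the SAP does not say that age-specific curves take precedence over the all-age curve. The cohort model names no interaction. The doubly robust sensitivity analysis (5.5.6) is only to be considered, and it adds confounder adjustment rather than effect modification.

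A reader might infer that the age mix will show up as waning. The SAP does not support that: it states neither an age gradient in effectiveness nor the age order of vaccination, and the reverse gradient hides waning. The mean ages in the descriptive table of 5.6.1 (36 in the unvaccinated, above 55 in the vaccinated columns shown) fit an older-first rollout but do not establish it. Nor does the SAP say that Objective 2 will be judged by comparing significant with non-significant subgroups; it is silent, and 6.1 requires confidence intervals.

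**Conclusion.** The point holds in two parts. Without condition, Objective 2 asks about difference, and the plan has no test of difference and no sex column in the table meant for pooling. Conditionally, the all-age matched curve can mimic or mask waning if effectiveness differs by age and vaccination was age-staged. Under the assumptions above the drift is about 0.02 to 0.07 on the RR scale, in either direction, and it is zero if either condition fails. The illustration combines both vaccines, whereas the plan stratifies by vaccine, so the vaccine-specific size is unknown.

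The consequence falls mainly on the 0.5 point-estimate rule: an upward drift of 0.02 exceeds BNT162b2's margin of 0.012. A reader might also conclude that the quadratic waning test is invalidated. Read as a between-arm contrast, it is hardly affected. If the coefficient is read as the exposed group's own time curve, staging alone gives expected z of 1.2 to 1.5 even with equal RRs, but that is a separate ambiguity about which coefficient is meant. This should be changed, but it does not undermine the design.

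**What to change.** - Add age group and exposure × age group to the matched weekly, spline and quadratic models, or state that the age-specific curves take precedence over the all-age curve, including for the 0.5 rule.
- Add a sensitivity analysis restricted to pairs whose recipient was vaccinated by 19 February 2021. This removes the effect of the fixed end date up to day 70, but not the loss of pairs when controls are vaccinated. Nations would supply the 5.6.4 table a second time for this subset.
- For Objective 2, pre-specify a low-dimensional exposure × time × subgroup test, such as a linear or quadratic time trend, one subgroup factor at a time. Adjust for age in the vaccine-type comparison.
- Add sex to the 5.6.4 table.

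The cost is a few model terms, one more column, somewhat wider intervals and low power for the interaction tests, given 541 recipient events from day 14. They should be reported with confidence intervals, and a non-significant result should not be read as similarity. A full month-of-dose interaction is not needed.

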4.2 Constructed variables

- Time to event in weeks (0-13, 14-20, 21-27, 28-34, 35-41, 42-48, 49-55, 56-62, 63-69 and 70+ days from dose 1, extend to 70-76, 77+ if numbers allow)
- Number of Q Covid risk groups (0,1,2,3,4,5+)
- Number of PCR tests in the pre vaccination era (0,1,2,3-4, 5-9, 10+). This will serve as our proxy for healthcare workers where healthcare worker status is unknown.
- Elderly care home resident (defined as person from a household with more than 10 people and an average age of over 65)

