We will assess vaccine waning using two different pre-specified approaches: first, conducting statistical hypothesis tests for declining effectiveness; and second, by assessing whether effectiveness is maintained above a minimum acceptable level. For the former, we will assess the curvature of the association in the spline modelled estimates over time, to evaluate whether the smoothed estimates peak and return to null. This will be achieved by fitting the same statistical model as for the spline but replacing the spline term with a quadratic term and post 14 days only. A statistically significant positive quadratic coefficient from this model in the exposed group would suggest waning. For the latter approach, we adopted the US Food & Drug Administration’s threshold of achieving a RR of at least 0.5 for the point estimate. [8]

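### The smoothing of the daily rate-ratio curve is left to unnamed software defaults; if these are the gam() defaults, REML would draw somewhat fewer false peaks at almost no cost

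*SAP*

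**What the plan says.** SAP section 5.5.2 specifies the smoother in one sentence: "thin plate regression splines (the R package ‘mgcv’ default settings"; from its last two words the sentence runs "default settings) with weekly knots from days 14 to the maximum week". The stated purpose is "to explore the timing of any waning of vaccine effectiveness". The difference between the two exposure groups' smooths then gives an RR for each day.

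The maximum week is not fixed. The time bands in section 4.2 end at "63-69 and 70+ days from dose 1, extend to 70-76, 77+ if numbers allow". Section 5.8 gives the R version, but the SAP names no mgcv fitting function, smoothing criterion or basis dimension.

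On waning, section 5.5.2 sets out to look at curvature "to evaluate whether the smoothed estimates peak and return to null". It says this is done by "replacing the spline term with a quadratic term and post 14 days only", with the rule "A statistically significant positive quadratic coefficient from this model in the exposed group would suggest waning".

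Sections 5.6 and 5.6.5 require every nation to supply the plot of the fitted curves.

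**The concern.** A curve used to date waning should not owe its bends to a software default. The SAP's wording lets two analysts fit different smoothers, because the default basis dimension is 10 while the number of weekly knots depends on a last day that is not stated. The word default also carries a choice of smoothing criterion. In mgcv, `gam()` uses GCV.Cp, which becomes UBRE for a Poisson model, while `bam()` uses fREML. UBRE tends to choose more flexible curves. When the true RR is constant, extra flexibility shows as a trough in RR followed by a rise, which a reader would see as effectiveness peaking and then waning.

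At stake are the exploratory curve, the timing read from it, and the plot that each nation submits. Event counts in single-vaccine or single-nation fits are modest, so spurious bends of visible size are more likely there.

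**Working it through.** **1. Knot counts.** Weekly knots from day 14 to day D number (D − 14)/7 + 1: 9 for D = 70, 10 for D = 77, 11 for D = 84, 17 for D = 126. Only D = 77 matches the default dimension of 10.

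**2. Software check (mgcv 1.9-3).** `gam()` accepted a weekly knot list with every other default unchanged. With 9, 11 or 17 knots the dimension stayed at 10 unless reset. Setting it equal to the number of knots changed the fit by less than 0.1% for D = 70, 77 and 84. In one simulated data set with D = 126, dimension 17 with weekly knots and the plain default gave clearly different curves (total effective df 4.3 against 10.3). One data set illustrates the point but does not measure it.

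**3. Inputs.** Events from day 14 in the SAP section 5.6.2 table, control/recipient: both vaccines 1,029/541; ChAdOx1 541/303; BNT162b2 488/238. Person-years implied by the printed rates for both vaccines are 1,029/0.0044 ≈ 234,000 and 541/0.0023 ≈ 235,000, so the crude RR is about 541/1,029 = 0.53.

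**4. Model.** For group g and day d: log E(y) = log(person-time) + a_g + s_g(d), with a rank-10 thin plate smooth per group, and RR(d) = exp{a_1 + s_1(d) − a_0 − s_0(d)}. Smoothness is chosen by UBRE = deviance/n + 2·edf/n − 1, or by REML. The true RR is constant. A false peak in effectiveness is an RR minimum at least 7 days from either end, with a stated minimum change on both sides. Assumptions not in the SAP: person-time halves every 21 days, and the baseline hazard is flat or wave-shaped.

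**5. Results.** 4,000 runs per row; UBRE v REML, % of runs; ratio from unrounded values in brackets.

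| Events, hazard, last day | Any interior peak | Change ≥10% | Change ≥25% |
|---|---|---|---|
| 1,029/541, flat, 77 | 25.2 v 18.5 (1.4) | 13.0 v 7.1 (1.8) | 4.6 v 1.6 (2.9) |
| 541/303, flat, 77 | 26.4 v 19.3 (1.4) | 15.7 v 8.9 (1.8) | 7.6 v 2.6 (2.9) |
| 488/238, flat, 77 | 26.5 v 20.1 (1.3) | 17.4 v 11.1 (1.6) | 9.4 v 4.3 (2.2) |
| 100/50, flat, 77 | 26.8 v 19.3 (1.4) | 21.7 v 14.2 (1.5) | 16.6 v 9.8 (1.7) |
| 1,029/541, flat, 125 | 25.6 v 18.8 (1.4) | 14.2 v 7.4 (1.9) | 5.5 v 1.5 (3.6) |
| 1,029/541, wave, 77 | 48.5 v 49.1 (1.0) | 31.4 v 30.2 (1.0) | 13.6 v 11.5 (1.2) |
| 541/303, wave, 77 | 48.4 v 47.6 (1.0) | 34.0 v 32.4 (1.0) | 18.5 v 16.3 (1.1) |

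The Monte Carlo SE for the first cell is √(0.252 × 0.748/4,000) = 0.7 percentage points. Mean total effective df was 5.5 v 4.6 in the first row, but 8.8 v 9.1 with the wave and the same counts. In the first row, an interior peak followed by a statistically significant rise occurred in 3.3% v 1.8% of runs.

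**6. Checks in mgcv itself.** 300 runs (1,029/541, flat): any interior peak 28% v 22%; ≥25%, 3.7% v 0.7% (imprecise). 200 runs per scenario (541/303, days 14–77): any interior peak 26% v 21% flat (1.2), 30.5% v 24.5% declining (1.2), 48% v 42% wave (1.1). REML had 4% to 11% lower RMSE for the log RR in all six scenarios run, and detected true waning nearly as often.

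**7. A different set-up.** 900 runs, days 14–97, hazard halving every 60 days; an interior minimum and a rise of at least 25% by day 70: 8.8% v 2.3% for 1,029/541, and 2.2% v 0.6% for 2,900/1,525, about UK scale. Absolute rates therefore depend heavily on the set-up. In these runs the pointwise 95% band missed the true RR on at least one day in 28–31% v 18–22% of runs; these band figures were not checked in a second simulation.

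**The case against.** The bracket about defaults follows the name of the basis and can be read as describing the basis only, with the knots specified separately. The software accepts that combination, and with the last day at 70 to 84 the result hardly depends on it. This stands: a reader might infer that the two settings exclude each other, but they do not. The wording is incomplete, not impossible to follow.

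The SAP never names `gam()`. An analyst using `bam()` would get fREML by default, and the modelling code that the SAP cites is not part of the document. This also stands, so the criticism of UBRE is conditional. That nations would in fact fit different smoothers is likewise possible but not shown: section 5.6.4 sets one common template of person-days and events and ties it to a meta-analysis program.

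The strongest objection concerns consequence. A reader might infer that undersmoothing biases the formal test for waning. It cannot, because that test replaces the spline by a quadratic term with no smoothing parameter. Nor is a 25% rise the return to null of which the SAP speaks: from a crude RR of 0.53 it reaches 0.53 × 1.25 = 0.66.

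Finally, a flat or log-linear hazard favours the heavier smoother, since the truth then lies in the unpenalised part of the spline. With a wave-shaped hazard the advantage in false peaks nearly vanishes. What remains is a consistent but modest gain in accuracy.

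**Conclusion.** The point holds as a cheap improvement to an exploratory analysis. If the `gam()` defaults are used, UBRE draws false peaks in effectiveness under a constant RR somewhat more often than REML. The ratio is about 1.1 to 1.4 for any interior peak. It is about 2 to 3 for changes of at least 25% when the log hazard is near linear (1.7 to 3.8 over all such set-ups run), and about 1.0 to 1.2 with a wave-shaped baseline. UBRE also gives slightly larger error in the log RR.

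A reader might take three times as a general figure. It is not: it appears near a 25% cut-off with a near-linear log hazard, and the SAP sets no cut-off. REML is also no full cure, since with a wave-shaped baseline both criteria drew a false interior peak in over 40% of runs. The shape of the curve should therefore not be read without intervals for the whole curve.

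The conclusion rests on assumed hazard shapes and person-time decay, on mgcv 1.9-3 and not the version used with R 3.6.1, and on event counts from the table in section 5.6.2.

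**What to change.** In SAP section 5.5.2, replace the reference to default settings with: smoothness selected by REML (`method = 'REML'` in `gam()`, fREML in `bam()`). State one fitting function, basis dimension, knot placement and last day, identical for all nations and vaccines. Where the shape of the curve is interpreted, preferably add simultaneous 95% intervals for the RR.

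The cost is one sentence in the SAP and a few arguments in the code. Sharp, short-lived features may be smoothed slightly more, and simultaneous bands are wider than pointwise ones. The quadratic test needs no change on this account.

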# 1. Introduction

The aim of this study is to determine whether protection from COVID-19 vaccination wanes after the first SARS-CoV-2 vaccine dose. At present, the vaccination programme in the UK uses two dose regimens of the Pfizer-BioNTech (BNT162b2) and the Oxford-AstraZeneca (ChAdOx1) vaccines. Whilst Moderna vaccine is now available in the UK, we will not include it in this analysis due to later start date and lack of follow-up data coverage. We theorise the vaccination programme as a natural experiment which has impacts that directly arise from the vaccination itself, as well as behavioural and other responses that occur as a consequence of broader programmatic effects - for example, being asked not to attend for vaccination if symptomatic and being reminded about protective behaviours to avoid infection.

We will use pseudonymised individual level linked routinely collected primary, laboratory and vaccination healthcare data across the UK nations. All data and analyses will be hosted within a trusted research environment within each nation. Pooled estimates will be calculated across the UK nations.

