### 5.5.5 Corrections for multiple testing

N/A

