# 6 Reporting results

## 6.1 Reporting guidelines and conventions

Results will be reported according to the Strengthening the Reporting of Observational Studies in Epidemiology (STROBE) and REporting of studies Conducted using Observational Routinely-collected Data (RECORD) (via the COVID-19 extension) guidelines. P-values will be quoted to two decimal places, unless they are less than 0.001 (whereby the p-value will be given as <0.001) or between <0.005 and >0.001, in which case they will be stated to three decimal places. Measures of association will be reported with 95% confidence intervals.

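### SAP 5.5.2 offers the comparison of the rate ratio with 0.5 as one of two unranked ways to assess waning, although it measures adequacy at a time point and not change

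*SAP*

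**What the plan says.** The Introduction states the question: "The aim of this study is to determine whether protection from COVID-19 vaccination wanes after the first SARS-CoV-2 vaccine dose". Section 5.5.2 answers it as follows: "We will assess vaccine waning using two different pre-specified approaches: first, conducting statistical hypothesis tests for declining effectiveness; and second, by assessing whether" protection stays above a set floor.

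- **Approach 1** is a test of change. A quadratic term in time replaces the spline, from day 14 on, and "A statistically significant positive quadratic coefficient from this model in the exposed group would suggest waning".
- **Approach 2** is a check of level. It adopts a regulator's "threshold of achieving a RR of at least 0.5 for the point estimate". No follow-up time is named for it, and no confidence-interval condition is attached.

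The text lists and describes the two. It does not call either primary, require both, accept either one, or say how opposite results are to be read. Section 5.5.5, "Corrections for multiple testing", is answered N/A. Section 5.5.3 adds an informal reading of weekly RRs in the whole cohort, also without a rule.

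**The concern.** Change and level are different quantities. Whether the RR rises with time since dose is a question of waning. Whether the RR at some time lies on the acceptable side of 0.5 is a question of adequacy. Section 5.5.2 places both under the assessment of waning.

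A vaccine with constant, modest effectiveness could then be described as failing a waning criterion, and one that had lost much of a high effectiveness as passing it. Correcting the form of the test or the direction of the threshold would not remove this, because a level still says nothing about change.

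**Working it through.** The SAP gives no design figure for the waning question, so there is none to reproduce.

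**Step 1: the two criteria on known curves.** Effectiveness is (1 − RR) × 100, as in section 5.5.3. The wording of the threshold runs opposite to a floor on effectiveness, so the floor is assumed to be intended and RR ≤ 0.5 is taken as met.

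- *RR constant at 0.56.* The log RR has zero slope and zero curvature, so nothing wanes. The threshold is missed because 0.56 > 0.5.
- *RR 0.35, then 0.15, then 0.42.* Effectiveness goes from 65% to 85% to 58%, a loss of 85 − 58 = 27 points from its best value. The threshold is met at the end because 0.42 ≤ 0.5.
- *RR rising log-linearly from 0.30 to 0.70.* Effectiveness falls from 70% to 30%. With s running from 0 to 1, log RR = log 0.30 + s·log(0.70/0.30), so the quadratic coefficient is exactly 0. The test as written has nothing to find, while the threshold is missed.

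**Step 2: how near the threshold the plan's own table lies.** The inputs are the composite events from day 14 in the matched-cohort table of section 5.6.2, with equal arm sizes. RR = vaccinated events / unvaccinated events; SE(log RR) = √(1/a + 1/b); the 95% CI is RR × exp(±1.96 SE).

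- ChAdOx1: 303/541 = 0.560; SE = √(1/303 + 1/541) = 0.0718; CI 0.487 to 0.645.
- BNT162b2: 238/488 = 0.488; SE = √(1/238 + 1/488) = 0.0791; CI 0.418 to 0.569.

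The printed rates give 2.2/4 = 0.55 and 2.4/5 = 0.48, so equal person-time is a fair approximation. Both intervals include 0.5.

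**Step 3: simulation.** Daily Poisson counts for days 14 to 76 (the SAP's bands run to "63-69 and 70+ days from dose 1, extend to 70-76, 77+ if numbers allow"), with 1029 control events (488 + 541) and 1,000 runs per row. A log-quadratic Poisson model is fitted by group. Waning is declared if z > 1.96 on the recipient-versus-control quadratic term. Section 5.5.2 states no significance level, so two-sided 5% is assumed from section 6.1: "Measures of association will be reported with 95% confidence intervals". The threshold is met if the fitted RR at day 76 is ≤ 0.5. Each cell shows events uniform over time / events with a 30-day half-life.

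| Assumed RR | Test declares waning | Threshold met | The two disagree |
|---|---|---|---|
| Flat 0.40 | 2.5 / 2.3% | 90.5 / 85.9% | 8.2 / 13.0% |
| Flat 0.56 | 2.2 / 2.2% | 25.1 / 29.0% | 72.7 / 68.8% |
| 0.35 → 0.15 → 0.42 | 98.0 / 97.1% | 81.9 / 76.1% | 79.9 / 73.2% |
| 0.30 → 0.70, log-linear | 2.6 / 2.8% | 1.2 / 4.8% | 96.2 / 92.4% |

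A coarser setup used nine weekly bands, 500 or 3000 control events, and the threshold judged on the last band. It gave the same picture. With a flat RR of 0.55 the threshold was missed in 57 to 76% of runs and the test was positive in 2 to 3%. With RR 0.40 → 0.15 → 0.45, waning on the test together with the threshold met occurred in 53 to 80%.

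**The case against.** The case for leaving the text alone has four parts.

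**The text already distinguishes the two.** Only the quadratic result is said to suggest waning. No sentence says that missing 0.5 means waning or that meeting it means none. This is correct, and it narrows the point to the shared label and the missing statement of what each result can conclude.

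**The formal aims are estimation aims.** Sections 2.1 and 2.2 ask for effectiveness by time since dose, and the main outputs are weekly RRs and a smoothed curve. Reporting both change and level is therefore defensible. This stands, but the Introduction still poses a yes-or-no question, and section 5.5.2 sets decision criteria for it.

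**A reader might infer that the authors could report whichever result suits them.** The documents do not support this. Both approaches are declared in advance, so dropping one would be a visible departure, and nothing permits reporting only one.

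**A reader might infer from the section 5.6.2 table that conflict is likely.** It does not follow. An average RR says nothing about trend. Both intervals span 0.5, and BNT162b2 is on the passing side. The ratios are crude and come from one nation (the footnotes use the Scottish deprivation index). That section also prints 1,650,185 matched first-dose recipients in one table and 2,573,874 in another, so the counts are weak evidence of what the planned analysis will show. The ratios show only that conflict is possible.

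The opposite overreach would be to make the quadratic test as written the sole decider. It detects a steady fall from 0.30 to 0.70 in only about 3% of runs, a decline that the threshold would flag.

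**Conclusion.** The concern holds in a limited form. Section 5.5.2 lists a level criterion among the ways to assess waning, gives neither approach precedence, and does not say what each may conclude. Step 1 shows, without any simulation, that the level criterion can be missed with no decline and met after a large one.

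The simulated disagreement runs from 8 to 13% (flat 0.40) to 92 to 96% (steady rise from 0.30 to 0.70). That range reflects the trajectories chosen, the equal person-time, the intended direction of the threshold and its evaluation at the end of follow-up, a time the SAP does not name. The percentages illustrate the mechanism and do not forecast the study. The conclusion rests on the wording of section 5.5.2.

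**What to change.** In section 5.5.2:

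1. State that the conclusion on waning rests on the change with time since dose in the recipient-versus-control RR, for the composite outcome in the matched cohort, UK-pooled and by vaccine.
2. Base it on a test of change that can also detect a steady decline, not on the quadratic coefficient alone. One option is a joint test of the linear and quadratic exposure-by-time terms, with the direction read from the fitted RR.
3. State that the comparison with 0.5 answers a separate secondary question, whether effectiveness is still adequate at a named time t, and that it neither establishes nor overrules waning.
4. State that both results are always reported, under separate headings.

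The cost is SAP wording and one further test from a model already planned; no new data are needed. There is a small downside: the threshold result can no longer be cited as evidence for or against waning.
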